### **5.2.2 Exclusion criteria**

1. Subjects who are, in the opinion of the investigator, mentally or legally incapacitated thus preventing informed consent from being obtained.
2. Subjects unable to perform or with contraindications to the tests proposed. In regard to respiratory tests, no respiratory infection or unstable condition will be noted in the last 4 weeks.

## **5.3 Measured parameters**

### **5.3.1. Measured parameters in pulmonary evaluation**

5.3.1.1 Respiratory symptoms questionnaire

5.3.1.2 Forced expiratory volume in 1 second (FEV1), forced expiratory flow (FEF25-75),

FEV1/FVC ratio and forced vital capacity (FVC)

5.3.1.3 PC20 methacholine

5.3.1.4 FVC and FEV1 after eucapnic hyperventilation.

5.3.1.5 Respiratory symptom scores (baseline and at 20% fall in FEV1 on methacholine and eucapnic hyperventilation challenges)

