### **2.1.2 Treatment of asthma in athletes**

Furthermore, asthmatic athletes seem often refractory to current asthma medications, including the frequently used inhaled  $\beta_2$  agonist. This medication does not seem to have performance enhancing effects when used at dose required to prevent or treat exercise-induced bronchoconstriction, their use has been regulated. To ensure that  $\beta_2$  agonist are used in confirmed case of asthma, the International Olympics Committee-Medical Commission (IOC-MC) has established criteria for a positive diagnosis of asthma. This criteria include a significant bronchodilatator response, or a positive bronchial provocation challenge, that is a fall in FEV1 of at least 10% from pre-challenge measures being required for exercise or eucapnic voluntary hyperventilation. Accordingly, Dickinson *et al.* looked at the difference in the prevalence of asthma in the 2000 and 2004 British Olympic Team. A similar prevalence of asthma was found; 21.2% in 2000 and 20.7% in 2004. However, 7 athletes without previous diagnosis of asthma tested positive to the bronchoprovocation test and 21% previously diagnosed with asthma did not meet the IOC-MC criteria. This suggest that some athletes take an asthma medication without indication and expose them to sanctions, as inhaled corticosteroids and  $\beta_2$  agonists are on the prohibited substances list (World Anti-Doping Agency). Indeed, athletes need a medical exemption and tests to prove they really need these medications. Athletes and coaches may use  $\beta_2$  agonists to improve their physical performances, but studies demonstrated that this medication, inhaled at current doses, does not enhances performance in well trained non-asthmatic athletes.

Asthma in the athletes population is probably an heterogeneous entity and some athletes may have an asthma-like condition. Specific studies on the prevalence of asthma, airway hyperresponsiveness, exercise-induced bronchoconstriction, inflammatory states and mechanisms are needed. At this time, little is known about the effects of long term high level training on respiratory health. Therefore, not only do we need to know more on the long-term effects of training, but the optimal management of these problems in high-level athletes with or without asthma need to be the subject of a specific respiratory monitoring.

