#### **3.2 Specific objectives**

- 3.2.1 Determine seasonal and long-term changes in airway caliber, airway responsiveness to methacholine and inflammation in high-level athletes involved in long-term intense training.
- 3.2.2 Evaluate the perception of respiratory symptoms after various airway challenges and evaluate if there is discordance between subjective and objective assessment.
- 3.2.3 Assess the efficacy of asthma medications in asthmatic athletes.

3.2.4 Assess R-R variability in high-level athletes overtime.

3.2.5 Assess cardiac activity in high-level athletes.

3.2.6 Evaluate maximal aerobic capacity in high-level athletes.

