**Eucapnic Voluntary Hyperventilation Test:** The method described by Argyros et al. will be used. Briefly, eucapnic hyperventilation consist in hyperventilating dry air containing 5% of CO2 at room temperature, during 6 min at 30 X baseline FEV1, i.e. 85% of maximal voluntary ventilation. FEV1 will be recorded before and 1, 3, 5, 10, 15 and 20 minutes after the test to see if bronchospasm appear. At 10% fall in FEV1 the tests is considered positive. Before each FEV1 manoeuver, the Borg score for perception of respiratory symptoms will be noted.

**Spirometric field testing:** FEV1 and FVC will be measured before and 1,5,10,15 and 20 minutes after maximal exercise to see if bronchospasm appear. At 10% fall in FEV1 the tests is considered positive. Before each FEV1 manoeuver, the Borg score for perception of respiratory symptoms will be noted. Exercise will be specific for each sport. Maximal exercise will be defined with maximal heart rate for each subject. The duration of exercise will be approximately 10 to 12 minutes.

**Induced sputum analysis:** Sputum will be obtained with hypertonic saline by the method described by Pin et al. and modified by Pizzichini et al. which involves inhaling increasing concentrations of saline (3, 4, and 5%) for seven minutes each through a mouthpiece without a valve or nose clip. Sputum processing will be performed as previously reported. Cytospins will be prepared. One cytospin will be dried and Wright-stained, and a 400 non-squamous cell differential will be performed. IS supernanant will be frozen in aliquots for delayed measurements of mediators and cytokines: VEGF, alpha-2 macroglobulin, ECP and MPO. Mucosal injury will be assessed by looking at the number of desquamated epithelial cells in the samples.

**Assessment of efficacy of asthma medication:** In the athletes who require a medication to treat asthma, we want to evaluate if the bronchodilators and inhaled corticosteroids are effective, as

they are in normal asthmatic (non-athletes). We will collect preliminary data, by analyzing the evolution of the respiratory symptoms following the medication administration. Afterwards, we will see if it is pertinent to make a controlled randomized studies.

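### The symptom score at a 20% FEV1 fall fits the titrated methacholine test, but is undefined for many athletes on the fixed-stimulus hyperventilation test, which is positive at 10%

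*Protocol*

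**What the plan says.** Section 5.3.1.5, in the list of pulmonary parameters, begins "Respiratory symptom scores (baseline and at 20% fall in FEV" and applies this point "on methacholine and eucapnic hyperventilation challenges". Two challenges therefore share one reference point.

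Section 4.4.1 describes the two tests differently:

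- **Methacholine** is given in concentrations up to 128 mg/ml, and the response is expressed as PC20.
- **Hyperventilation** is one exposure, "during 6 min at 30 X baseline FEV" (times 30, that is, a set ventilation target). FEV1 is read before the test and at minutes 1, 3, 5, 10, 15 and 20. The rule for a positive result is "15 and 20 minutes after the test to see if bronchospasm appear. At 10% fall in FEV", followed by "the tests is considered positive". Section 2.1.2 gives the same threshold as background: a fall "of at least 10% from pre-challenge measures being required for exercise or eucapnic voluntary hyperventilation".

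On hyperventilation, before each FEV1 manoeuvre, "the Borg score for perception of respiratory symptoms will be noted". Methacholine and the field test have an equivalent Borg rule.

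Objective 3.2.2 is to study perception after several kinds of airway challenge and to "evaluate if there is discordance between subjective and objective assessment". It sets no fall threshold.

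**The concern.** A score at a 20% fall needs a test that either drives the athlete to 20% or is stepped until that point is reached. Methacholine titration does this in responders. A single hyperventilation bout does not: each athlete falls by whatever amount follows, and the protocol already calls the test positive at half the fall that the score requires.

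Read as written, an athlete with a 15% fall has a positive test and no post-challenge symptom score under 5.3.1.5. So does an athlete with marked symptoms and a 5% fall, whose test is negative. The first may be a positive test that goes unnoticed, the second a symptom without obstruction. Both are discordance in the sense of objective 3.2.2, and the first also bears on hypothesis 4.1, that problems often go unrecognised.

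The second risk is analytic freedom. Each hyperventilation test yields several Borg and FEV1 pairs. If the stated reference point does not work, the analyst could choose among the 10% point, the 20% point, the lowest FEV1 or a slope after seeing the results.

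**Working it through.** **Step 1: set the definitions side by side.**

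| | Methacholine | Eucapnic hyperventilation |
|---|---|---|
| Stimulus | Stepped, up to 128 mg/ml | One 6-minute bout |
| Result expressed as | PC20 | Positive at a 10% fall |
| Score point in 5.3.1.5 | 20% fall | 20% fall |
| Is that point built into the test? | Yes, for responders | No |
| Borg taken | Before each FEV1 | Before each FEV1 |

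For hyperventilation the score is undefined below a 20% fall. Above 20% it is not unique either: FEV1 is read at six fixed times and may cross 20% once while falling and again while recovering.

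**Step 2: what is collected.** Readings per hyperventilation test = 1 baseline + 6 post-challenge = 7. For 100 athletes, 100 × 7 = 700 planned Borg and FEV1 pairs per round, whatever the fall.

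**Step 3: how many athletes would have the score as defined.** The protocol gives no rate for a 20% fall on hyperventilation, and its sample of 100 has no calculation behind it, so there is no figure to reproduce. The following is an illustration only.

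Formula: number with a score = 100 × P(fall ≥ 10%) × P(fall ≥ 20% given fall ≥ 10%).

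- The first factor uses proxies from the protocol's background, none of them a hyperventilation rate in this cohort: 20.7% (asthma prevalence in the 2004 British Olympic team, section 2.1.2); 35% (43/124 = 34.7% of skaters falling more than 10% after exercise, section 2.1.4); 55% (top of the quoted asthma range in athletes, section 2.1).
- The second factor is purely assumed: 10%, 25% or 50%.

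| P(fall ≥ 10%) | 10% assumed | 25% assumed | 50% assumed |
|---|---|---|---|
| 20.7% | 2.1 | 5.2 | 10.3 |
| 35% | 3.5 | 8.8 | 17.5 |
| 55% | 5.5 | 13.8 | 27.5 |

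The range is about 2 to 28 of 100.

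Positive tests without the score = 100 × P(fall ≥ 10%) × (1 − second factor). This runs from 20.7 × 0.5 = 10.4 to 55 × 0.9 = 49.5, and is 35 × 0.75 = 26.3 in the middle case.

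**Step 4: precision.** If the score were correlated with another measure (the protocol does not specify such an analysis), the 95% half-width on the Fisher z scale is 1.96/√(n − 3):

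- n = 9: 1.96/√6 = 0.80
- n = 28: 1.96/√25 = 0.39
- n = 100: 1.96/√97 = 0.20

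**The case against.** The strongest reply is that this is an unclear line in a list of measurements. A reader might infer that objective 3.2.2 would be answered only in the few athletes who fall by 20% or more, with the rest dropped. The protocol does not support that:

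- Section 4.4.1 takes Borg before every FEV1 manoeuvre in every athlete.
- Section 5.3.1.7 lists field-test perception with no fall threshold.
- Methacholine contributes scores at a point that suits that test.
- No text makes 5.3.1.5 the sole measure for the objective or excludes anyone from it.
- No figure in the protocol shows that few athletes reach 20% on hyperventilation.

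All of this stands, and it limits the point to the definition of one parameter.

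It can also be argued that the 20% attaches to methacholine only. The grammar permits this, but it does not rescue the item, because hyperventilation would then have a baseline score and no stated post-challenge point.

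A third argument is that scoring perception at a common degree of obstruction is a coherent design, and that athletes who do not reach PC20 necessarily lack that score. This stands for methacholine, where no change is needed. A 20% fall without symptoms is also discordant, and the present item captures it.

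Leaving the matter to a statistical analysis plan is a weaker reply. The protocol has not left the reference point open; it has stated one that does not match its own test.

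**Conclusion.** The point holds as a defect of definition. Section 5.3.1.5 fixes a hyperventilation symptom score at a fall that the test in section 4.4.1 is not built to reach and that is twice its own positivity threshold. The score is undefined for every athlete below 20%, including positive tests between 10% and 20%, a group relevant to objective 3.2.2.

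Its size is minor to moderate: it affects one parameter for one of several challenges, and all the underlying data are already planned. The figure of roughly 2 to 28 of 100 athletes with the score rests on borrowed prevalence and exercise-test rates and on an assumed conditional share. It shows the scale of the problem and is not an estimate. The mismatch itself follows from the text and does not depend on these assumptions.

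**What to change.** Reword section 5.3.1.5 so that each challenge has its own reference point:

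- **Hyperventilation:** Borg score at baseline and at the lowest post-challenge FEV1, in every athlete tested, reported together with the percentage fall at that reading and by the 10% positivity result.
- **Methacholine:** keep the score at baseline and at the 20% fall.

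The field-test item needs no repair on this account. A within-athlete slope of Borg on percentage fall is optional; it would be poorly determined in athletes whose FEV1 hardly changes, so it should not replace the score at the lowest FEV1.

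The cost is one line of protocol wording. No extra visit, test or reading is needed, because Borg is already taken before each manoeuvre. The change should be made before the perception data are analysed.

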5.3.1.6 Induced sputum eosinophils/neutrophils and cytokines analysis

5.3.1.7 FVC and/or FEV1 + perception of symptoms (Borg) after an intense training session (field-test).

### **5.3.2 Measured parameters in cardiovascular evaluation**

5.3.3.1  $\text{VO}_2$  max

5.3.3.2 Significant clinical changes in electrocardiogram

5.3.3.3 Blood pressure response to exercise

5.3.1.4 24h monitoring of blood pressure

5.3.1.5 Heart rate variability

5.3.1.6 Anthropometric parameters by bioimpedance (percentage of body fat)

5.3.1.7 Other measures such as cardiac size, stroke volume and cardiac output (echography) are usually done in athletes for clinical purpose, these will be obtained for additional analysis.

### **5.3.3. Measured metabolic parameters**

5.3.3.2 Significant and systemic markers of inflammation (C-reactive protein, fibrinogen)

5.3.3.3 Complete blood formula

5.3.3.4 Serum cholesterol (CHOL), high-density lipoprotein-cholesterol (HDL-C), low-density lipoprotein-cholesterol (LDL-C), triglycerides (TG), apo B, apo A and glucose level.

5.3.3.5 Ferritin, serum iron, percentage of saturation , saturation capacity

5.3.3.6 Creatin kinase (CK), ions, urea, creatinin

5.3.3.7 Surfactant associated protein A or B (SP-A, SP-B)

5.3.3.8 Cytomegalovirus and Epstein-Barr virus

## **4.4 Description of the Methods (a summary of investigation can be found on appendix 1)**

### **4.4.1. Pulmonary evaluation**

**Questionnaires and asthma control assessment:** Apart from current subjects' characteristics (age, sex, duration of asthma, etc.), current respiratory symptoms will also be reported according to The European Community Respiratory Health Survey (ECRHS). Outdoor and indoor training duration will be also noted.

**Physical Examination:** A cardio-thoracic examination including blood pressure will be performed at the baseline visit.

**Allergy skin prick tests:** Atopy will be determined using skin prick tests to a battery of common aeroallergens. Normal saline and histamine will be used as negative and positive controls respectively. Skin wheal diameter will be recorded at 10 min as the mean of 2 perpendicular measurements. A positive response will be defined as a skin wheal diameter of 3 mm or more.

**Spirometry:** FEV1, FVC and FEF25-75% will be measured from flow-volume curves performed according to the American Thoracic Society (ATS) specifications. Predicted values will be obtained from European Respiratory Society (ERS). The baseline FEV1 will be calculated as the best of three reproducible values (with maximum change of 5%). Spirometry will be performed with an ATS approved spirometer.

**Methacholine challenge:**

- Methacholine responsiveness will be measured using the “classical” tidal volume method described by Juniper. Briefly, concentrations of methacholine up to 128 mg/ml will be used. Response will be expressed as the PC20 methacholine. Before each FEV1 manoeuvre, the Borg score for perception of breathlessness will be recorded. FVC will also be noted at baseline and after the lowest post-methacholine FEV1.
- During the visit 1, the methacholine challenge is performed after the eucapnic voluntary hyperventilation challenge. During the visit 7, the same methacholine challenge is performed but without previous eucapnic voluntary hyperventilation challenge.
- During the visit 8, a single-dose methacholine test will be performed. Baseline FEV1 will be measured in triplicate and the lowest baseline value will be retained to estimate the percentage fall of FEV1. There will be no saline inhalation. The dose of methacholine chosen for the test will be the final dose that will have induce a 20% fall in FEV1 on methacholine of the visit 7. FEV1 will be measured only at 3 and 4 minutes from the end of the inhalation. At the end of the inhalation, the patient will continue to avoid deep inspiration for three minutes after which the first FEV1 will be obtained.
- During visit 9, the same test as in visit 8 will be performed, except that after baseline measures of FEV1, the inhalation of a single dose of methacholine will be preceded by 20 minutes of deep inspiration avoidance. During that period, the athletes will avoid any deep inspiration including sneezing, coughing, laughing or any abnormal respiratory movement for 20 minutes before the onset of the inhalation of the single dose of methacholine. To ensure that no deep inspiration will be taken, the respiratory volume will be checked with a pneumotachograph.

**Eucapnic Voluntary Hyperventilation Test:** The method described by Argyros et al. will be used. Briefly, eucapnic hyperventilation consist in hyperventilating dry air containing 5% of CO2 at room temperature, during 6 min at 30 X baseline FEV1, i.e. 85% of maximal voluntary ventilation. FEV1 will be recorded before and 1, 3, 5, 10, 15 and 20 minutes after the test to see if bronchospasm appear. At 10% fall in FEV1 the tests is considered positive. Before each FEV1 manoeuver, the Borg score for perception of respiratory symptoms will be noted.

**Spirometric field testing:** FEV1 and FVC will be measured before and 1,5,10,15 and 20 minutes after maximal exercise to see if bronchospasm appear. At 10% fall in FEV1 the tests is considered positive. Before each FEV1 manoeuver, the Borg score for perception of respiratory symptoms will be noted. Exercise will be specific for each sport. Maximal exercise will be defined with maximal heart rate for each subject. The duration of exercise will be approximately 10 to 12 minutes.

**Induced sputum analysis:** Sputum will be obtained with hypertonic saline by the method described by Pin et al. and modified by Pizzichini et al. which involves inhaling increasing concentrations of saline (3, 4, and 5%) for seven minutes each through a mouthpiece without a valve or nose clip. Sputum processing will be performed as previously reported. Cytospins will be prepared. One cytospin will be dried and Wright-stained, and a 400 non-squamous cell differential will be performed. IS supernanant will be frozen in aliquots for delayed measurements of mediators and cytokines: VEGF, alpha-2 macroglobulin, ECP and MPO. Mucosal injury will be assessed by looking at the number of desquamated epithelial cells in the samples.

**Assessment of efficacy of asthma medication:** In the athletes who require a medication to treat asthma, we want to evaluate if the bronchodilators and inhaled corticosteroids are effective, as

they are in normal asthmatic (non-athletes). We will collect preliminary data, by analyzing the evolution of the respiratory symptoms following the medication administration. Afterwards, we will see if it is pertinent to make a controlled randomized studies.

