### **2.1.6 Swimmers in indoor pools**

**It has been previously shown that deep inspiration avoidance and time intervals between inhalation and measurement of FEV1 influence methacholine challenges in normal subjects but not in asthmatic nor in obese subjects. We would like first to verify if doing the eucapnic hyperventilation test before the methacholine challenge could influence the FEV1 fall after the methacholine. Secondly, we would like to verify if deep inspiration avoidance before inhalation could enhance the fall in FEV1 after the methacholine challenge, as previously reported.**

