**4.5. Deep inspiration avoidance before methacholine inhalation enhances the fall of FEV1 in athletes.**

## **5. METHODS**

### **5.1 Study design**

Visits will be done by athletes to the laboratory on 2 occasions each year over a period of at least 3 years and field-tests at 2 times per year according to the annual planning schedule of each team, including 1 testing during competing season and 1 in the resting period. (For example, speed skaters begin their season in September and their resting period is in the month of April.) On the

first visit, consent form will be explained by the investigator or his/her delegate and signed by the subject. At the first visit, physical examination, medical questionnaire regarding their health condition, their family history of disease, their medication and their history in practicing their sport will be performed. Also, respiratory questionnaire, blood sample, eucapnic hyperventilation test, allergy prick skin test, methacholine challenge with Borg score and sputum analysis will be done, as well as the Holter. At the second visit maximal aerobic capacity test and MAPA will be done. At the third visit, spirometric field testing will be performed for each sports. Visit 4, 5 and 6 will be the same as visit 1, 2 and 3, except for allergy test which will be done only on the first visit.

| Visits                                 | 1 | 2 | 3 | 4 | 5 | 6 | 7 | 8 | 9 |
|----------------------------------------|---|---|---|---|---|---|---|---|---|
|                                        |   |   |   |   |   |   | X |   |   |
| Reading and signature of the assent    | X |   |   |   |   |   |   |   |   |
| Physical exam                          | X |   |   | X |   |   |   |   |   |
| Medical questionnaire                  | X |   |   | X |   |   |   |   |   |
| Anthropometric parameters              |   | X |   |   | X |   |   |   |   |
| VO2max test with ECG                   |   | X |   |   | X |   |   |   |   |
| Blood sample                           | X |   |   | X |   |   |   |   |   |
| Respiratory questionnaire              | X |   |   | X |   |   |   |   |   |
| Eucapnic hyperventilation test         | X |   |   | X |   |   |   |   |   |
| Allergy tests                          | X |   |   |   |   |   |   |   |   |
| Methacholine test + Borg score         | X |   |   | X |   |   | X | X | X |
| Induced sputum                         | X |   |   | X |   |   |   |   |   |

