| Spirometric field testing              |   |   | X |   |   | X |   |   |   |
| Holter (heart rate variability)        | X |   |   | X |   |   |   |   |   |
| MAPA (24hre blood pressure monitoring) |   | X |   |   | X |   |   |   |   |

**In an addition, volunteer athletes will have three supplementary visits during the summer season, inside 10 days (visit 7, 8 and 9). These three visits will include different methacholine challenge protocols. The first methacholine challenge (visit 7) will be the same than in the first visit of the excellence protocol (see Table above, standard Juniper protocol), but no**

eucapnic voluntary hyperventilation challenge will be performed before. During the visit 8, a single-dose methacholine will be performed without previous deep inspiration during 20 minutes before the first inhalation. During the visit 9, a single-dose methacholine will be performed without deep inspiration avoidance. These protocols were previously used in asthmatic, control and obese subjects (Simard et al. 2005, Boulet et al. 2005).

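### Visit 7, the only standard methacholine challenge without prior hyperventilation, is confined to summer, while its implied comparator, visit 1, follows team calendars, so a hyperventilation effect cannot be separated from season and elapsed time

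*Protocol*

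**What the plan says.** The purpose of the supplement is given in the second of the two protocol sections headed as concerning swimmers in indoor pools (2.1.6): "We would like first to verify if doing the eucapnic hyperventilation test before the methacholine challenge could influence the" fall in FEV1 after methacholine. Deep inspiration avoidance is the second question.

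Section 4.4.1 (Methacholine challenge) describes the two conditions one after the other. With hyperventilation: "During the visit 1, the methacholine challenge is performed after the eucapnic voluntary hyperventilation challenge". Without it: "During the visit 7, the same methacholine challenge is performed but without previous eucapnic voluntary hyperventilation challenge". The outcome of the standard challenge is PC20 ("Response will be expressed as the PC"20).

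Section 5.1 fixes the timing. The supplement consists of "three supplementary visits during the summer season, inside 10 days (visit 7, 8 and 9"). Routine testing instead follows each team's annual plan, "including 1 testing during competing season and 1 in the resting period", with speed skaters as the example: season starting in September, rest in April. Visit 4 repeats visit 1 apart from the allergy test, and testing runs for at least three years.

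Objective 3.2.1 is to "Determine seasonal and long-term changes in airway caliber, airway responsiveness to methacholine and inflammation" in the same athletes. Hypothesis 4.3 is that long-term intense training goes with an increase in airway responsiveness.

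**The concern.** In the visit table, visit 7 is the only standard challenge without hyperventilation on the same day. Visits 8 and 9 are single-dose tests and cannot take its place. The supplement's first question can therefore be answered only by setting visit 7 against a hyperventilation-preceded test. Sections 4.4.1 and 5.1 both describe visit 7 by reference to visit 1, so visit 1 is the natural reading.

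The two tests differ in more than hyperventilation. One is always in summer and the other falls wherever the team's calendar puts it. Training phase can differ and the time between them is open. If responsiveness changes with season or accumulated training, which the protocol sets out to investigate, that change enters the contrast in full. It could be reported as a hyperventilation effect, or it could cancel a real one.

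**Working it through.** **What the contrast estimates.** The protocol states no figure for this comparison, so there is none to reproduce. On the log2 PC20 scale, write h for the hyperventilation effect, s for the effect of season and training phase, and d for drift with elapsed time. Then

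expected (visit 1 − visit 7) = h + [s(visit 1) − s(summer)] + [d(visit 1) − d(visit 7)].

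Only h is wanted. The two bracketed terms vanish only if both tests fall in the same season and close together, and nothing in section 5.1 or 4.4.1 requires that.

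**The schedule side by side.**

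| Test | Prior hyperventilation | Timing |
|---|---|---|
| Visit 1 | yes | team calendar |
| Visit 4 and later repeats | yes (repeat of visit 1) | team calendar |
| Visit 7 | no | summer, within 10 days of visits 8 and 9 |

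Every standard test without hyperventilation is in summer, and no test with it is placed there by design.

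**How far apart the tests can be.** I take summer as June to August (my assumption) and use the protocol's example months. If visit 1 is in September, the next summer is 9 to 11 months later. If it is in April, the gap is 2 to 4 months. The nearest hyperventilation-preceded test on that calendar is closer: for June, April is 2 months away; for July, September is 2 months away; for August, September is 1 month away. Choosing the nearest test rather than visit 1 can thus cut the gap from as much as 11 months to at most 2.

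**What an unmatched shift could do.** The inputs are assumptions, because section 4.5 gives only 100 athletes overall. True hyperventilation effect zero; a seasonal shift of 0.25, 0.5 or 1.0 doubling common to all volunteers; paired SD 1.0 or 1.5 doublings; n of 10 to 40; two-sided paired t-test at 0.05. The noncentrality is shift × √n / SD; for a shift of 0.5, n = 20 and SD 1.5 it is 0.5 × 4.47 / 1.5 = 1.49. The probability of a false positive is then:

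| SD | n | shift 0.25 | shift 0.5 | shift 1.0 |
|---|---|---|---|---|
| 1.0 | 10 | 0.11 | 0.29 | 0.80 |
| 1.0 | 20 | 0.19 | 0.57 | 0.99 |
| 1.0 | 40 | 0.34 | 0.87 | >0.99 |
| 1.5 | 10 | 0.08 | 0.16 | 0.47 |
| 1.5 | 20 | 0.11 | 0.29 | 0.81 |
| 1.5 | 40 | 0.18 | 0.54 | 0.98 |

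**A milder case.** Suppose half the volunteers happen to have visit 1 in summer. The mean shift halves, and the variance becomes SD² + 0.5 × 0.5 × shift². With n = 20 and SD 1.0, the probabilities fall to 0.08, 0.18 and 0.48. With both conditions tested in one short window in varied order, the shift cancels on average and the rate returns to 0.05.

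**The case against.** The strongest reply is that the comparison is inferred. No sentence says that visit 1 PC20 will be compared with visit 7 PC20, and the hyperventilation question is neither a numbered objective nor a hypothesis; 3.2.7 and 4.5 concern deep inspiration avoidance only. The analysis could also use visit 4 and later repeats, giving hyperventilation-preceded tests on both sides of the summer visit. All of this is fair. It limits the importance of the point and supplies most of the remedy, but it does not remove the problem: the question is stated, visit 7 is the only test that can answer it, and no near comparator is named. A season term in a later analysis plan could not cleanly repair it either, since it would depend on whichever athletes happened to have a hyperventilation-preceded test in summer.

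Several stronger readings are tempting and are not supported:

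- A reader might infer that the protocol expects a seasonal shift. Objective 3.2.1 only sets out to determine whether there is change, and hypothesis 4.3 concerns long-term training. No seasonal size or direction is asserted.
- A reader might infer that this comparison decides whether the routine PC20 values can be trusted. The protocol does not say so. Visits 1, 4 and their repeats all include hyperventilation, so within-athlete change across them compares like with like if any hyperventilation effect is constant. At most the absolute PC20 level is in question.
- A reader might infer that visit 7 always comes after the hyperventilation-preceded tests. That holds for visit 1, going by the visit numbering, but visit 4 or a later repeat may follow the summer visit.
- The use of volunteers limits generalisability. It does not in itself bias a within-person difference.

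**Conclusion.** The point holds as one of design: as scheduled, the visit 1 versus visit 7 contrast cannot isolate the effect of hyperventilation from season, training phase and elapsed time. That conclusion rests on the visit schedule alone, together with the inference that visit 1 is the comparator.

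The size of the bias is not known. The false-positive rates above depend on an assumed common shift, SD and number of volunteers, and fall when athletes' calendars differ. They show that a modest shift could matter and say nothing about whether one exists.

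The damage is confined to the supplement's first question. Objective 3.2.7 is untouched, because visits 8 and 9 draw on visit 7 and not on visit 1. The change should be made, but the main follow-up programme does not depend on it.

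**What to change.** In sections 5.1 and 4.4.1:

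1. Name the comparator for visit 7 as the hyperventilation-preceded challenge closest in time, and in the same training phase where possible. This may be visit 4 or a later repeat, or the mean of the tests bracketing the summer visit, instead of visit 1 by default. Bracketing removes steady drift only when the tests are roughly evenly spaced, and would not remove a change peculiar to summer.
2. Where calendars allow, place visits 7 to 9 within a few weeks of such a test. On the example calendar, late August followed by a September test might achieve this without leaving summer. Vary which comes first only around visit 4 or later repeats, since consent and baseline assessment take place at visit 1.
3. Where no near test exists, report the contrast as exploratory and not as a hyperventilation effect, and use visit 7 only as the reference for visits 8 and 9.

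No extra tests are needed. The cost is in scheduling: visits 7, 8 and 9 are tied within 10 days and must move together, some supplementary visits may fall outside summer, and some athletes will not contribute to this comparison.
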